### Subjects and eligibility criteria

The corrective exercise specialist (Ph.D.) primarily screens the subjects recruited through invitation letters from private and public organizations in Tehran, Iran, for three main UCS features. Since the presence of scapular dyskinesia may indicate the lack of neuromuscular control, including muscle activation and timing thus, the related tests are performed to evaluate the position and rhythm of the scapula, which plays a significant role in facilitating the upper extremity function among office workers [58–60]. Further, due to any postural alteration influencing the muscle activity, muscle length and muscle strength tests are implemented for UT and pectoral muscles and MT, LT, and deep cervical flexor, respectively [61].

Inclusion criteria for the trial must comply with office workers between 30 and 45 years using a computer or lab-tops most commonly during the working day (about 30 h per week) with at least 5 years of experience [17, 62]. Having alignment alteration includes forward head (≥ 45°), round shoulder (≥ 52°), and round back (≥ 42°) according to previous studies [63, 64]. Marking pain intensity score visual analog scale (VAS) ≥3 in neck and shoulder [17, 58, 65].

Concerning exclusion criteria, those are ineligible if pregnant during the study process, having surgery on the upper extremities during the past year, unable to perform exercise due to any medical conditions, and being in weight out of the normal range (18 ≥ BMI ≥ 25).

Drop out criteria are considered if the subjects attend no post-tests, lose three sequential intervention sessions, and any factors that may affect the study results.

However, the subjects are allowed to discontinue the study at any stage [66]. At the first encounter at baseline, the researchers are asked for permission to contact them in the case of study discontinuation. Accordingly, performing an accurate intention-to-treat analysis of the primary result is possible.

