### Randomization

The subjects will be randomized to one of the two treatments and control groups including workplace exercise, online-supervised exercise, and control using https://www.sealedenvelope.com. Randomization will be performed as block randomization with a 1:1 allocation. A sufficient number of the subjects will be recruited according to the sample size calculation to minimize random error. Meanwhile, to ensure the allocation concealment, the randomization code will not be released until the subject has been recruited into the trial, which occurs after all baseline measurements. Therefore, randomization will be performed through a computer-generated sequence for allocation concealment, including concealed, sequentially numbered, sealed, and opaque envelopes. A card inside indicates the allocated group to each subject [67].

The trial investigator will implement the various stages of the randomization process and enrollment and assign the subjects to interventions. The SBU professor assistant will supervise all the procedures implemented by the investigator, including the sequence generation process and allocation concealment mechanism during the study process to ensure that the assignment schedule is unpredictable and locked away from even the person who generated it.

The trial process is not independent of the investigators. The professor assistant (correspondent author) from SBU frequently supervises the procedures for auditing trial conducting a periodic independent review of core trial processes and documents. Auditing contains the participant enrolment, consent, eligibility, and allocation to study groups, adherence to trial interventions and policies to protect participants, including reporting of harms and completeness, accuracy, and timeliness of data collection.

A formal amendment to the protocol will be agreed upon by the Iranian Registry of Clinical Trials (IRCT), including any modifications to the protocol which may impact the conduct of the study, a potential benefit of the subjects, or may affect their safety, including changes of study objectives, study design, study population, sample sizes, study procedures, or significant administrative aspects. Meanwhile, the Ethics Committee on the Research will approve such an amendment at SBU, Tehran, Iran. The trial investigators are responsible for the decision to amend the protocol.

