### Sample size

Based on the results of the previous studies and a pilot study, 11 subjects are calculated for each group using G*Power software (version 3.0.10, Germany) with an alpha level of 0.05, power (1 − β) of 80%, and effect size of 0.66. It should be noted that the effect size was reported in the previous study that investigated the effects of corrective exercises on neck pain between the intervention and control groups [41]. However, to avoid the probability of losing the subjects during the research process, the number is considered 15 in every three groups (*N* = 45 subjects).

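### The drop-out criteria end in an undefined clause that permits removal after randomisation and conflicts with the intention-to-treat statement beside it

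*Protocol article*

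**What the plan says.** All but two of the statements are in the Protocol article, under Subjects and eligibility criteria.

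- Drop-out list, first two items: "Drop out criteria are considered if the subjects attend no post-tests, lose three sequential intervention sessions".
- Drop-out list, third item: "and any factors that may affect the study results".
- Exclusion criteria: "those are ineligible if pregnant during the study process".
- Following paragraph: participants are asked at baseline to allow contact if they discontinue, so that "performing an accurate intention-to-treat analysis of the primary result is possible".

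Under Randomization, the article says: "The trial investigator will implement the various stages of the randomization process and enrollment and assign the subjects to interventions". The same section adds: "The trial process is not independent of the investigators".

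The section on statistical methods names a 3 × 2 mixed ANOVA and an ANCOVA of the post-test on the pre-test. It names no analysis set. The article does not mention blinding.

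**The concern.** The first two drop-out items are facts that anyone can check. The third is not: almost any prognostic event, change in activity or poor response could be said to affect the results. It is a stated criterion that can operate after randomisation, so a fuller document could add detail but the published rule would remain.

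It also does not fit the intention-to-treat sentence. If that sentence governs, the clause should take nobody out of the analysis. If the clause governs, intention to treat is not delivered. Even on the kinder reading, the sentence covers only the primary result, so alignment, workability and EMG are left without it.

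The pregnancy wording raises the same question, because an event during the study is made a ground of ineligibility and its effect on the analysis is not stated.

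With 15 per arm, one person carries 1/15 = 6.7% of an arm's mean. Baseline adjustment does not correct removals that depend on the outcome.

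**Working it through.** **1. The plan's own figures.** Sample size section: alpha 0.05, power 80%, effect size 0.66, 11 per group, raised to 15 for losses. The metric of 0.66 is not stated. Read as Cohen's f for two groups, the noncentrality is 2n × f². For n = 11 this is 22 × 0.4356 = 9.58, giving power 0.837. For n = 10 it is 20 × 0.4356 = 8.71, giving power 0.797. So 11 reproduces on that reading. The allowance is 15 − 11 = 4 per arm, or 4/15 = 26.7%. A few discretionary removals would therefore look like the attrition already expected.

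**2. Set-up of the check.** Three arms of 15 with no true effect. Post-test = ρ × pre-test + √(1 − ρ²) × e, where pre-test and e are standard normal. ρ = 0.5 is an assumption, because the article gives no SD or correlation. The analysis is ANCOVA with a common slope and pooled residual, with 45 − 3 − 1 = 41 degrees of freedom before removals. The contrast is one exercise arm against control, two-sided at 0.05, with 20,000 runs. The people removed are those with the most extreme baseline-adjusted residuals, so the selection is the worst possible for each pattern.

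| Removed | Two-sided error | Error favouring exercise | False shift (SD) |
|---|---|---|---|
| None | 5.1% | 2.6% | 0 |
| Least favourable one from each exercise arm | 8.1% | 6.4% | 0.11 |
| Least favourable two from each exercise arm | 11.8% | 11.1% | 0.20 |
| One from each exercise arm plus the most favourable control | 13.0% | 12.2% | 0.22 |

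Repeat runs agree within 0.6 of a percentage point; for the second row they gave 7.5% and 7.6%.

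**3. Hand check of the shifts.** The expected largest of 15 standard normal values is 1.736 and the second largest is 1.248 (from 15 × ∫ x φ(x) Φ(x)¹⁴ dx and its counterpart for the second). The residual SD is √0.75 = 0.866.
- One removed: 1.736/14 × 0.866 = 0.11 SD.
- Two removed: (1.736 + 1.248)/13 × 0.866 = 0.20 SD.
- One from exercise and one from control, in opposite directions: 2 × 0.107 = 0.21 SD.

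**4. How far the result depends on the selection.** In a simpler two-group t test with 15 per arm:
- Removal unrelated to outcome: 5.0%.
- Worst responders removed from both arms alike: 6.9% (one each) and 8.4% (two each).
- Removal from one exercise arm only: 7.3% (one) and 11.0% (two).

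At the other extreme, a two-arm ANCOVA with ρ = 0.5 and removal on change score, in opposite directions in the two arms, gave 10.7% with one per arm and 23.7% with two.

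**5. Selection on a factor only partly related to outcome.** The patterns of step 2 were repeated with removal on a factor correlated with the adjusted outcome (the correlation is an assumption). Error was 5.2% to 5.4% at correlation 0.3, and 5.7% to 6.6% at 0.5 with shifts of 0.06 to 0.11 SD.

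**The case against.** Five points can be made for the plan.

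- **The text does not say that a drop-out leaves the analysis.** Contact after discontinuation is arranged so that intention to treat can be done. If it is done, a person caught by the clause still counts for both primary outcomes. This stands, and it is why one cannot say that the clause breaks the comparison for every outcome. What remains is that the analysis is only called possible, is limited to the primary result, and is not reconciled with the drop-out list.
- **A reader might infer that unblinded investigators can remove people at will.** The article is silent on blinding and does not say who applies the clause. What it supports is narrower: the investigator who assigns participants knows the arm, and the process is not independent of the investigators. The Randomization section also provides for periodic review of enrolment, eligibility, adherence and data completeness. That review is done by the corresponding author, so it is a limited safeguard, but it is one. The ethics section also commits to reporting protocol deviations.
- **A reader might infer that one removal per exercise arm more than doubles the error.** It does not: the two-sided rate is about 8%, or 1.6 times nominal. Doubling needs the heavier patterns in the table, chosen on the observed outcome.
- **Removal in good faith has a much smaller effect.** Step 5 bears this out. Bias is present, but error stays well short of double.
- **The neighbouring criteria concern participation, not outlying results.** This is a fair reading. Nothing says that the clause is applied after post-test values are seen, but nothing rules it out.

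**Conclusion.** The concern holds in a limited form. The article states an open-ended ground for dropping randomised participants, in a trial whose investigator makes the assignments, and does not reconcile it with its own intention-to-treat statement. That defect is in the text and needs no simulation.

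The size is an upper bound: from 5% to about 8% with one worst-case removal per exercise arm, and about 12% to 13% with two per exercise arm or with one per exercise arm plus one control. These figures assume normal outcomes, ρ = 0.5, removals chosen on the baseline-adjusted outcome, and removed people being absent from the analysis. If removals are unrelated to outcome, or if intention to treat is in fact applied to the primary outcomes, that inflation does not arise for those outcomes. The secondary outcomes have no such protection in the text.

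The pregnancy wording is a matter of reconciling two statements, not an error of known size.

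**What to change.** - Delete the open clause from the drop-out criteria.
- State that all randomised participants are followed and analysed as allocated, for primary and secondary outcomes. Non-analysis is then limited to withdrawal of consent or a post-test that could not be obtained. Missing three sessions in a row is recorded as adherence, not used as a route out of the analysis.
- Record any other factor thought to matter and, if wanted, handle it in a sensitivity analysis listed before the data are seen.
- Reconcile the pregnancy wording with the intention-to-treat statement, so that an event after randomisation is kept separate from removal from the analysis. The clinical handling of such an event is for the investigators, and no rule is proposed here.

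The cost is a few sentences of wording and continued follow-up of people who stop, for which permission is already sought. The downside is that a few atypical participants stay in and add a little noise.

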### Randomization

The subjects will be randomized to one of the two treatments and control groups including workplace exercise, online-supervised exercise, and control using https://www.sealedenvelope.com. Randomization will be performed as block randomization with a 1:1 allocation. A sufficient number of the subjects will be recruited according to the sample size calculation to minimize random error. Meanwhile, to ensure the allocation concealment, the randomization code will not be released until the subject has been recruited into the trial, which occurs after all baseline measurements. Therefore, randomization will be performed through a computer-generated sequence for allocation concealment, including concealed, sequentially numbered, sealed, and opaque envelopes. A card inside indicates the allocated group to each subject [67].

The trial investigator will implement the various stages of the randomization process and enrollment and assign the subjects to interventions. The SBU professor assistant will supervise all the procedures implemented by the investigator, including the sequence generation process and allocation concealment mechanism during the study process to ensure that the assignment schedule is unpredictable and locked away from even the person who generated it.

The trial process is not independent of the investigators. The professor assistant (correspondent author) from SBU frequently supervises the procedures for auditing trial conducting a periodic independent review of core trial processes and documents. Auditing contains the participant enrolment, consent, eligibility, and allocation to study groups, adherence to trial interventions and policies to protect participants, including reporting of harms and completeness, accuracy, and timeliness of data collection.

A formal amendment to the protocol will be agreed upon by the Iranian Registry of Clinical Trials (IRCT), including any modifications to the protocol which may impact the conduct of the study, a potential benefit of the subjects, or may affect their safety, including changes of study objectives, study design, study population, sample sizes, study procedures, or significant administrative aspects. Meanwhile, the Ethics Committee on the Research will approve such an amendment at SBU, Tehran, Iran. The trial investigators are responsible for the decision to amend the protocol.

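### One investigator role generates the sequence, runs the concealment, enrols and assigns, so concealment from the enrolling investigator is not secured, despite the claim that the schedule is locked away from its generator

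*Protocol article*

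**What the plan says.** All the relevant text is in the Randomization section of the protocol article.

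- **Roles.** "The trial investigator will implement the various stages of the randomization process and enrollment and assign the subjects to interventions".
- **Supervision.** An assistant professor, who is also the corresponding author, is to "supervise all the procedures implemented by the investigator, including the sequence generation process and allocation concealment mechanism". The stated purpose is that the "assignment schedule is unpredictable and locked away from even the person who generated it".
- **Independence.** "The trial process is not independent of the investigators". The same assistant professor audits enrolment, eligibility and allocation, among other things.
- **Safeguards.** The sequence is computer-generated, with sealedenvelope.com named as the tool. Cards are placed in "concealed, sequentially numbered, sealed, and opaque envelopes". In addition, "the randomization code will not be released until the subject has been recruited into the trial, which occurs after all baseline measurements".
- **Scheme.** "Randomization will be performed as block randomization with a 1:1 allocation". No block size is given. The Sample size section gives 15 in each of three groups, 45 in total.

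**The concern.** Allocation concealment has to hold against one person above all: whoever decides whether the next candidate enters the trial, and when. Here that person has the same role as the one who generates the sequence and implements the concealment.

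Someone who knows or can guess the next allocation can hurry, delay or discourage an enrolment, perhaps without intending to. An example is bringing in a well-motivated candidate when an exercise arm is next. Eligibility leaves some room for this, since being unable to exercise because of a medical condition is a matter of judgement.

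Each participant is 1/15, or about 7%, of an arm, so a few steered enrolments can move an arm mean. Both primary outcomes, pain on a visual analogue scale and days of sick leave from a single questionnaire item, are reported by the participant. Differences in motivation between arms could therefore pass directly into the results.

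**Working it through.** **Step 1: set the statements side by side.**

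1. The investigator implements the stages of randomisation, enrols and assigns.
2. The procedures that the investigator implements include sequence generation and the concealment mechanism.
3. The schedule is locked away from the person who generated it.

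From 1 and 2, the generator and the enroller are the same role. Statement 3 could then hold only if someone else took custody of the list and prepared or released the allocations. The section names nobody for this. The assistant professor supervises and audits, but is not said to hold the list or the envelopes. The online service is named as the means of randomising, while the described release is by cards in envelopes. The three statements do not fit together as written.

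**Step 2: ask what each safeguard protects against.** Opaque numbered envelopes and release after baseline work against participants and against staff who have not seen the list. They do not work against the person who produced the list and runs the envelope procedure. Supervision and periodic audit oversee that person but do not separate the tasks.

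**Step 3: size of the exposure.** The plan gives no figure to reproduce. The inputs are N = 3 × 15 = 45 and equal allocation to three arms, both from the article. The block size is assumed.

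*Case A: the enroller has seen the list.* All 45 allocations are foreseeable.

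*Case B: the list is hidden, but past allocations are known and blocks are fixed and of known size.* Let each arm have c places in a block of 3c. An allocation is certain once only one arm has places left, that is, within the final run of a single arm.

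- The expected length of a final run from a given arm is c/(2c + 1), because its c places fall among 2c + 1 gaps around the other 2c.
- Over three arms this is 3c/(2c + 1) per block.
- The share of allocations that are certain is therefore 1/(2c + 1).

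| Block size | c | Share certain | Of 45 | Best guess correct |
|---|---|---|---|---|
| 3 | 1 | 1/3 | 15 | 61% |
| 6 | 2 | 1/5 | 9 | 56% |
| 9 | 3 | 1/7 | 6.4 | 53% |
| 12 | 4 | 1/9 | 5 | 51% |
| 15 | 5 | 1/11 | 4.1 | 50% |

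The last column comes from exact enumeration of each block. For blocks of 3 it is (1/3 + 1/2 + 1)/3 = 0.611. Chance is 33%. Blocks of 6 and 12 do not divide 45 evenly, so their counts are the share applied to 45. At the extreme, a single block of 45 would leave 1/31, or about 1.5 of 45, certain.

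**The case against.** The strongest reply is that the article lists the usual protections: a computer-generated sequence, sealed opaque numbered envelopes, release only after baseline, supervision of generation and concealment, and an audit of allocation. How the schedule is locked away is operational detail that a condensed article may leave to the full protocol. This carries weight against any claim about what will happen. It does not answer the contradiction, which lies in what the section states about roles and not in what it omits.

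Several stronger readings are tempting, and the documents do not support them.

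- A reader might infer that concealment is defeated. The stated safeguards count for something, and nothing says that the investigator will consult the list. The text shows only that concealment from the enroller is not secured.
- A reader might infer that the enroller keeps the envelopes. No custodian is named.
- A reader might take the trial as declared open. Blinding is not stated. That past allocations are evident is an inference, though a probable one, from a control group that receives no intervention.
- A reader might conclude that no analysis could repair the damage. The planned ANCOVA uses each pre-test value as covariate, so it addresses measured baseline severity. It does not address unmeasured motivation or prognosis.
- A reader might object to a 1:1 ratio in a three-arm trial. With 15 per group, equal allocation is plainly meant, and this is only a point of wording.

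The block figures are also conditional. The section does not exclude varying block sizes, and blocks of 3 are the worst case.

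**Conclusion.** The point holds as a contradiction in the Randomization section with a practical consequence: as written, the schedule is not protected from the person who enrols. It should be corrected, but it does not show that allocation was or will be subverted.

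The exposure is all 45 allocations if the enroller has seen the list. If the list is hidden, about 4 to 15 of 45 are certain in advance for blocks of 15 down to 3. That range assumes fixed blocks, a block size and boundaries known to the enroller, and past allocations that are visible. The first two are assumptions and the third is inferred from the arms. The role conflict itself needs none of them. Sample size, alpha and power are unaffected.

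**What to change.** Reword the role sentence; do not delete it, because it is where the section says who enrols and assigns. The new text should state that:

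- an existing team member with no part in enrolment generates and holds the 1:1:1 list, with randomly varying block sizes, and controls the envelopes. Alternatively, the already named sealedenvelope.com service does this through central release;
- the investigator enrols, and receives each code only after the participant's ID has been logged and baseline is complete. Release after baseline is already planned, so the ID log is the new element;
- if the assistant professor becomes the list holder, that person does not enrol (the article does not say this now), and another existing team member reviews the allocation records, so that nobody audits their own work.

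The running cost is one short message per participant and a transfer of tasks within the team. Because the section sends changes to study procedures through the trial registry and the ethics committee, a formal amendment may also be needed. The Trial status section places the study at the enrolment stage, and the change protects only participants not yet randomised. For any already allocated, the trial report should say who generated the list and who held it and the envelopes.
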